### Ethics

This trial has been approved by the Human Research Ethics Committees of Guangdong Second Provincial General Hospital (2017-FS-032). This trial has been registered at the Chinese Clinical Trials Registry: ChiCTR1800014465. All study participants will be provided with written consents prior to participation. Written informed consent has been obtained from the patients for publication of this manuscript and accompanying images. All study-related information will be securely protected at the study site.

### Quality assurance and monitoring

To ensure that the study is of a high quality, all study procedures will be conducted in compliance with the protocol in the principles of the Good Clinical Practice (GCP) provided by the International Conference on Harmonization [24]. The researchers will learn to perform the study properly via a 2-day training workshop. They will also be given a written protocol and standardized intervention content documents. A detailed explanation of the study and a task form (Fig 4) will be provided to participants. Moreover, the outcome assessors will be blinded to group assignment.

**Fig. 3 Fig3:**
[figure not shown]
The satisfaction survey of Guangdong Online Hospital (GOH)

**Fig. 4 Fig4:**
[figure not shown]
Task form for the conventional therapy plus a brief Guangdong Online Hospital intervention (CT-GOH) group (above) and the conventional therapy (CT) group (below)

**Fig. 5 Fig5:**
[figure not shown]
The schedule of enrollment, interventions, and assessments

The study progress and research data will be consistently monitored by an Independent Data Monitoring Board (IDMB), which will be independent from the study organizers. The IDMB will examine trial procedures, facilitate compliance with the study protocol, and ensure the data quality and safety.

### Withdrawal

Participants are free to withdraw from the study at any time, which will be informed during the consent process. If a participant chooses to withdraw, they will be asked to provide reasons and the reasons for withdrawal will be recorded. Besides, participants can discontinue the study at any time point if they experience any adverse events. The adverse events will be recorded.

### Planned statistical analysis

To evaluate the feasibility of the study, we will calculate the proportion of enrolled participants out of all eligible patients, participants who adhered to the intervention and the dropout rates. Besides, a patient satisfaction survey for the use of GOHT will be collected and analyzed.

Means and standard deviations will be used to describe between-group statistics of WOMAC, MFI, HADS and PSQI. All these variables will be analyzed using a repeated-measures mixed-effect model with terms for age, sex, Body Mass Index and treatments. The measurement data will be assessed for normal distribution using Shapiro-Wilk’s test for both groups. Independent samples’ *t* test will be used for the comparison of two-independent samples. Non-parametric tests (Mann-Whitney *U* test) will be used in cases of abnormal distribution. Statistical analysis will be processed by SPSS software (version 19.0). The categorical variables will be compared by a chi-square test. *P* < 0.05 will be accepted as the threshold for statistical significance.

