## Methods/design

### Trial design

This study is a prospective, parallel randomized controlled trial (RCT) conforming to Standard Protocol Items: Recommendations for Interventional Trials (SPIRIT) guidelines (Additional file 1) [15]. The flow chart of the participants is illustrated in Fig. 1. This study will be carried out in our hospital (Fig. 2). The total duration of the study is expected to take approximately 12 months depending on the process of enrollment and follow-up visits. Both groups will be followed up for 6 months.

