### Sample size

This pilot study will be conducted without performing a formal sample size calculation, as the primary outcome is the feasibility of GOHT in the enhanced management for patients with OA. We plan to recruit 20 participants for each group, allowing for a 20% dropout over the period. As the recommended sample size for a feasibility pilot trial is 12 per group [19], we anticipate that the sample size of 40 participants will provide us with sufficient information about the feasibility of the intervention including the enrollment rate and the acceptability of the intervention.

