### Randomization and blinding

Recruited participants will be randomly allocated to either the CT-GOHT group (intervention) or the CT group (control) at a 1:1 ratio. Random numbers will be generated using a computer software program run by an external statistician. Each of the random numbers with the group assignment will be written on a piece of paper and packed in a sealed envelope. After baseline assessment, participants will be provided an envelope according to the randomization sequence. The outcome assessors will be blinded to the participant randomization assignment.

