### Intervention group (CT-GOHT group)

In addition to conventional therapy (celecoxib, 0.2 g daily), participants in the CT-GOHT group will receive a brief repeated GOH-based management every month via the GOHT platform. The web-based management is expected to last 20–30 min for an independent intervention, containing three broad segments: encouragement, educational lectures and medical issues. The clinicians who perform the intervention have received standardized training and should be familiar with the process and the detailed contents of an intervention. To ensure standardized interventions for each participant, standard operating procedures will be provided for the researches.

Participants will be required to attend follow-up clinics at 2 weeks, 3 months and 6 months after the initiation of the trial. When the symptoms get worse, participants will be allowed to get further treatment at any time.

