### Outcome assessments

The outcome assessments will be made at baseline, 2 weeks and 3 month later after the initiation of the study and at the end of 6 months. All measurements of participants will be performed by a researcher blinded to the group allocation.

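### The listed terms of the secondary-outcome mixed model omit baseline score, visit and treatment-by-visit, so its treatment effect is either diluted or less precise than it need be, and is not tied to a visit

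*Protocol article*

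**What the plan says.** Under *Planned statistical analysis* the protocol article describes the four questionnaires by group ("Means and standard deviations will be used to describe between-group statistics of WOMAC, MFI, HADS and PSQI") and then fixes the model: "All these variables will be analyzed using a repeated-measures mixed-effect model with terms for age, sex, Body Mass Index and treatments". The same section also names a t test or Mann-Whitney test for two-sample comparisons, without saying at which visit.

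Other sections set the context:

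- *Outcome assessments* gives four measurement times, the last at 6 months: "The outcome assessments will be made at baseline, 2 weeks and 3 month later".
- *Randomization and blinding* puts allocation after the first of these: "After baseline assessment, participants will be provided an envelope according to the randomization sequence".
- *Intervention group (CT-GOHT group)* gives the frequency of the intervention: "participants in the CT-GOHT group will receive a brief repeated GOH-based management every month via the GOHT platform".
- *Sample size* gives the numbers: "We plan to recruit 20 participants for each group, allowing for a 20% dropout over the period".
- *Discussion* says that the preliminary effect data are to inform power calculations for larger trials.

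No section says whether the baseline score is a response, a covariate or unused in the model, and none names a main time point for the secondary outcomes.

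**The concern.** A repeated-measures model whose only treatment-related term is a main effect estimates one average difference over whichever visits are entered as responses. Two of the four visits are poor candidates for that average. Baseline precedes allocation, so the expected difference there is zero. At 2 weeks, with monthly sessions, few or none will have been delivered.

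There are two ways to read the sentence, and each has a cost. With baseline among the responses, the average is pulled towards zero. With baseline left out, a score that has been collected and is probably the best predictor of later scores goes unused. On both readings the model has no term from which a 3-month or 6-month difference can be read.

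What is at stake is the effect information for the next trial. An estimate that is too small because of the model, or wider than it need be, is a poor basis for that planning.

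**Working it through.** **Inputs from the article.** There are four visits, allocation follows baseline, sessions are monthly, and 20 per group are planned with 20% dropout. That leaves 20 × 0.8 = 16 completers per group. The article gives no SD, correlation, effect size or power, so there is no figure of the plan's own to reproduce.

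**Assumptions.** SD 1 at every visit, equal correlation r between any two visits (0.5 to 0.7), complete balanced data for 16 per group, and two-sided 5%. Where power is shown, the true 6-month effect is set at 0.8 SD.

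**1. What the treatment term estimates.** With balanced data it is the plain mean of the visit-specific differences. As a share of the 6-month effect:

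| Effect pattern (baseline, 2 weeks, 3 months, 6 months) | Four visits as responses | Three post-baseline visits |
|---|---|---|
| Constant: 0, 1, 1, 1 | 3/4 = 75% | 3/3 = 100% |
| From 3 months only: 0, 0, 1, 1 | 2/4 = 50% | 2/3 = 67% |
| Linear in time: 0, 0.083, 0.5, 1 | 1.583/4 = 40% | 1.583/3 = 53% |

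A simulation of mixed models (300 runs, 20 per arm, r = 0.5, constant true effect 0.80) agrees. The treatment term averaged 0.59 on four visits and 0.79 on three. A model with baseline, visit and treatment-by-visit gave 0.81 at 6 months.

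**2. Precision.** SE = √(2/n × V), where V is:

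- four-visit mean: (1 + 3r)/4
- three-visit mean, unadjusted: (1 + 2r)/3
- three-visit mean, baseline-adjusted: (1 + 2r)/3 − r²
- 6-month contrast, baseline-adjusted: 1 − r²

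| r | Three-visit V, unadjusted | Three-visit V, adjusted | Variance ratio | 6-month adjusted V | 6-month SE, n = 16 |
|---|---|---|---|---|---|
| 0.5 | 0.667 | 0.417 | 1.6 | 0.75 | 0.306 |
| 0.6 | 0.733 | 0.373 | 2.0 | 0.64 | 0.283 |
| 0.7 | 0.800 | 0.310 | 2.6 | 0.51 | 0.252 |

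**3. Power, non-central t, 16 per group.**

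| Scenario | r | Listed terms, four visits | Listed terms, three visits | Baseline-adjusted post-baseline mean | Baseline-adjusted 6-month contrast |
|---|---|---|---|---|---|
| Constant 0.8 SD | 0.5 | 55% | 76% | 92% | 72% |
| Constant 0.8 SD | 0.6 | 50% | 72% | 95% | 78% |
| 0.8 SD from 3 months only | 0.6 | 26% | 40% | 67% | 78% |

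Baseline adjustment always helps the average. A 6-month contrast gains clearly when the effect comes late. When the effect is constant, it is about level with the listed terms on three visits: slightly better at r = 0.6 and slightly worse at r = 0.5.

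**4. The missing visit term.** If both arms have the same pattern of observed visits, a shared time trend cancels from the treatment difference and only adds residual noise. It does not cancel when missing data differ by arm. Simulations with a shared 0.8 SD improvement, baseline as a response and 0% versus 40% dropout gave a spurious difference of about 0.10 SD (0.08 to 0.12). With visit in the model it was zero within simulation error.

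**The case against.** The best defence is that a journal article condenses the full plan. The sentence does not claim to be exhaustive, and calling the model repeated-measures presupposes that visit indexes the rows. This stands in part: the article does not show which of the two readings would be fitted. But it is not silent on the model. It lists fixed effects down to BMI, and indexing rows by visit does not put visit or its interaction among them.

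Other objections limit how far the point can be pushed. A reader might infer any of the following, and the documents do not support them:

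- *The treatment effect is necessarily diluted.* With three post-baseline responses and a constant effect it is not.
- *The model halves the power, 50% against 95%.* That pairs the worst reading with the adjusted post-baseline average. For a 6-month contrast under a constant effect, the comparison on the three-visit reading is 72% against 78% at r = 0.6, and 76% against 72% at r = 0.5.
- *Omitting visit biases the result.* It does so only if missing data differ by arm. The article allows for 20% dropout and suggests no split between arms, so the 0.10 SD figure rests on an assumed 0% versus 40%.
- *The plan can give no 6-month comparison.* The t test or Mann-Whitney test could be run at 6 months, although the text does not say so and it would be unadjusted.
- *The trial's main result is at risk.* The primary outcome is feasibility, and there was no formal sample size calculation. Group SDs, which also feed power calculations, do not depend on this model.

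**Conclusion.** The point holds in a conditional form. As listed, the model has one of two weaknesses, depending on how baseline enters:

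- **Baseline as a response:** dilution to 75% of a constant effect, or 50% of one that starts at 3 months.
- **Baseline left out:** no dilution of a constant effect, but a variance about 1.6 to 2.6 times the adjusted variance, and 67% of an effect absent at 2 weeks.

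In both cases it yields no visit-specific difference. The percentages follow from the visit schedule once an effect pattern is assumed. The variance ratios rest on the assumed correlation of 0.5 to 0.7 and equal SDs.

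The omission is certain from the text. The size of its effect in this trial is not, because the article gives no SD, correlation or effect pattern. Only secondary outcomes of a 40-participant feasibility pilot are touched, so this should be fixed but is not critical.

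**What to change.** Replace the model sentence with wording such as: *For each scale, the 2-week, 3-month and 6-month scores are the responses. Fixed effects are baseline score, visit (categorical), treatment, treatment-by-visit, age, sex and BMI, with within-participant correlation modelled. The baseline-adjusted difference between groups with its 95% CI is reported at 2 weeks, 3 months and 6 months, together with the average over the post-baseline visits.*

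Reporting both the visit-specific differences and the average matters, because a single-visit contrast can be less precise than the average when the effect is constant, while the average understates a late effect.

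The cost is wording and a few degrees of freedom. All the variables come from the planned assessments or are already in the model, no visits or participants are added, and SPSS fits the model. *Trial status* describes the trial as pending at submission, so as of that date the change could be made before any outcome data were seen.

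### On the natural reading, the four clinical scales get both a mixed model and a t or Mann-Whitney test picked by a normality pre-test, and the plan does not say which result prevails

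*Protocol article*

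**What the plan says.** All the relevant text is in one paragraph of the protocol article, Planned statistical analysis.

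- It plans means and standard deviations for WOMAC, MFI, HADS and PSQI, and then states: "All these variables will be analyzed using a repeated-measures mixed-effect model with terms for age, sex, Body Mass Index and treatments". Neither the baseline score nor visit is among these terms.
- The next sentence begins "The measurement data will be assessed for normal distribution using" and names the Shapiro-Wilk test, applied to both groups. No level is given for it.
- The independent-samples t "test will be used for the comparison of two-independent samples", and the Mann-Whitney test "will be used in cases of abnormal distribution".
- One threshold covers the whole paragraph: P < "0.05 will be accepted as the threshold for statistical significance".

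The paragraph does not say which variables or visits the two-sample tests serve, whether they use raw or change scores, or whether they or the model give the reported treatment effect.

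Elsewhere, Outcome assessments sets measurements at baseline, 2 weeks, 3 months and 6 months. Primary outcome measures makes feasibility the primary outcome, so the four scales are secondary. The Discussion expects the effect information to serve power calculations for later trials.

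**The concern.** The paragraph prescribes two inferential routes for what appear to be the same measurements, and one of them depends on the observed data.

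First, the t test compares means and the Mann-Whitney test compares ranks. If a pre-test picks between them separately for each comparison, the compared quantity can differ from one scale or visit to the next for no clinical reason.

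Second, with no order of precedence, whoever reports the trial may take either result as the finding for a scale. Two chances at P < 0.05 are more than one.

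Third, the baseline score is the obvious covariate for repeated scales in a small trial. It is collected but appears in neither route. What is at stake is a single, comparable effect estimate per scale, which a later trial would want from this pilot.

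**Working it through.** **Inputs from the protocol article.** Sample size: "We plan to recruit 20 participants for each group, allowing for a 20% dropout over the period". Completers per arm: 20 × (1 − 0.20) = 16. There is no power-based figure to reproduce, since "This pilot study will be conducted without performing a formal sample size calculation". There are four instruments and three post-baseline visits. The threshold is 0.05, taken as two-sided.

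**Assumptions, since the article gives none.** Shapiro-Wilk is run at 0.05 in each arm, and a rejection in either arm leads to Mann-Whitney. Correlation between visits is equal for all pairs, at 0.3 to 0.7. Scores are normal, gamma or lognormal. The mixed-model treatment effect is represented by a t test on each patient's mean over visits, its equivalent for balanced data, without age, sex and BMI.

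**1. How often the pre-test switches the method (16 per arm, simulated).**

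| True distribution | Switched to Mann-Whitney |
|---|---|
| Normal | about 9% (theory: 1 − 0.95² = 0.0975) |
| Gamma, shape 4 | 40-42% |
| Gamma, shape 2 | 67% |
| Lognormal, log-scale SD 0.6 | 78-79% |

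**2. Type I error of the pre-test route alone.** At 6 months with no true effect, the selected test rejects in 0.048 to 0.054 of trials, over normal and lognormal data and correlations 0.3 to 0.7. That is essentially nominal.

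**3. Type I error with two unranked tests per outcome.**

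| Tests available for one outcome | Correlation | Chance of at least one P < 0.05 under no effect |
|---|---|---|
| Model + selected 6-month test, normal data | 0.3 / 0.5 / 0.7 | 0.083 / 0.079 / 0.073 |
| Model + selected 6-month test, lognormal data | 0.3 / 0.5 / 0.7 | 0.085 / 0.082 / 0.069 |
| Model + t tests at all three post-baseline visits, normal data | 0.5 / 0.6 / 0.7 | 0.134 / 0.126 / 0.113 |

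The last row uses plain t tests, without the pre-test.

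**4. How often the two routes disagree.** With an assumed true difference of 0.8 SD at every post-baseline visit, the model and the selected 6-month test reach different significance verdicts in 16% to 30% of trials. Part of this is expected: the model averages over visits and the two-sample test looks at one. That is itself a reason to say which question is the intended one.

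**5. Baseline adjustment.** Power at 6 months for the same 0.8 SD:

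| Data | Correlation | Selected test, unadjusted | Baseline-adjusted linear model |
|---|---|---|---|
| Normal | 0.3 / 0.5 / 0.7 | 0.58 / 0.59 / 0.59 | 0.61 / 0.70 / 0.85 |
| Lognormal | 0.3 / 0.5 / 0.7 | 0.80 / 0.79 / 0.78 | 0.67 / 0.72 / 0.85 |

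Adjustment helps throughout with normal data. With skewed data it helps only at the highest correlation. If the model keeps baseline as one of the repeated outcomes and tests only a treatment main effect, which the listed terms permit, its power with normal data is 0.66 / 0.55 / 0.46.

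**The case against.** The strongest reply is that the sentences on normality name no scale and no visit. The mixed model is the only between-group analysis tied by name to the four instruments, and the t, Mann-Whitney and chi-square sentences could be a generic description, perhaps of baseline characteristics. An article also condenses, and a fuller plan may settle precedence. Part of this stands: the wider scope is an inference. But the sentences follow the scales without a change of subject, concern continuous data compared between groups, and share the significance threshold. Nothing limits them to baseline. What is criticised is a rule the article states, not a detail it omits.

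A reader might also infer four stronger things, which the documents do not support.

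- *That the pre-test inflates the error rate.* It does not: 0.048 to 0.054. The excess comes from having more than one unranked test, and its size depends on how many visits are tested, which the article does not state.
- *That a Mann-Whitney result leaves no mean difference for later power calculations.* The same paragraph plans means and standard deviations for all four scales, so those inputs survive whichever test is used.
- *That ignoring baseline costs a fixed amount of precision.* A variance ratio of 1/(1 − 0.6²) = 1.56 requires a correlation of 0.6, which is assumed. With skewed data the unadjusted selected test had more power at correlations 0.3 and 0.5.
- *That a switch somewhere is likely even with normal data.* 1 − (1 − 0.0975)¹² = 0.71 assumes 4 × 3 = 12 independent gated comparisons. The article does not specify 12, and correlated visits are not independent. A switch is also not in itself a wrong conclusion.

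**Conclusion.** The point holds in a limited form. On its natural reading, the paragraph gives each of the four scales a mixed-model result and a two-sample result chosen by a normality pre-test, with no order between them. The pre-test makes the compared quantity depend on the sample. The per-outcome chance of a false positive rises from 5% to about 7-8% with one 6-month test beside the model, or 11-13% if all three post-baseline visits are tested, at correlations 0.5 to 0.7. Neither route, as listed, includes the baseline score, and the model lists no visit term. The precision lost cannot be fixed from the article, because it gives neither the correlation nor the distribution.

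These figures rest on 16 completers per arm, equal correlations and the assumed shapes. Severity is moderate: the scales are secondary outcomes of a 40-patient feasibility pilot, and the feasibility results are untouched.

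**What to change.** Revise the paragraph as follows.

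- Make one mixed model per scale the only between-group analysis of WOMAC, MFI, HADS and PSQI, with baseline score, visit, treatment and treatment-by-visit, plus the age, sex and BMI terms already listed.
- Report adjusted mean differences with 95% confidence intervals, alongside the means and standard deviations already planned.
- Drop the Shapiro-Wilk step and the t and Mann-Whitney comparisons for these scales. Alternatively, state that they apply only to baseline characteristics, or label them descriptive.
- Check the model residuals graphically. If they are clearly non-normal, add a bootstrap confidence interval for the same adjusted difference as a sensitivity analysis.

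The cost is small: a few more model terms, a residual check and possibly a bootstrap run. No new data are needed, because baseline scores are already collected. If the two-sample tests were meant only for baseline characteristics, one clause saying so resolves the precedence question, but the model would still need its baseline and visit terms.
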